##### Data collection

For this aim, we will recruit, enroll, and collect data from a longitudinal cohort of PWH (*N* = 1800); data will be collected at baseline and at 12-, 24-, and 36-month follow-up. We will implement the Mobile Patient Technology for Health (mPATH™) in the clinic. mPATH™ is a patient-facing digital health platform allowing patients to confidentially answer routine ambulatory screening questions [51]. At the time of ambulatory visit check-in, patients are provided a tablet by front desk staff with mPATH™ that includes standard clinic assessments of fall risk, depression, and anxiety, and incorporates the 2-item Hunger Vital Sign measure [52, 53], which measures household food insecurity over the prior 12 months. Because people at risk of food insecurity often have other unmet social needs, mPATH™ also assesses housing stability and transportation barriers (Table 1) [54]. The mPATH™ platform offers data collection in English or Spanish. If a participant is unable to effectively utilize mPATH™, a clinic staff member will assist by reading the items to the participant. Data from mPATH™ flows directly into the participant’s EHR.

**Table 1 Tab1:** Study measures

Domain	Measures and citations	Data source
*Aim 1 and Aim 2*		
Prediabetes or T2DM (primary outcome)	Fasting and non-fasting glucose, A1C level, diagnosis codes (ICD-10), current diabetic medications (including glucagon-like peptide 1 agonist, sodium-glucose cotransporter 2 inhibitor, dipeptidyl peptidase 4 inhibitor, sulfonylurea, incretin mimetic, or insulin)	EHR data extraction (baseline, 12mo, 24mo, 36mo)
Hypertension, hyperlipidemia, obesity, and elevated waist circumference (secondary outcomes)	History of high blood pressure, current blood pressure-lowering medications, 3 most recent systolic and diastolic blood pressure readings, history of high cholesterol, current cholesterol-lowering medications, lipid panel (total, LDL, HDL, triglycerides), body-mass index, waist circumference	EHR data extraction (baseline, 12mo, 24mo, 36mo)
Food insecurity	2-item Hunger Vital Sign [50, 51]	EHR data extraction (baseline, 12mo, 24mo, 36mo)
Basic demographics	Age, race, ethnicity, gender, sexual orientation, insurance status, preferred language, zip codes	EHR data extraction (baseline, 12mo, 24mo, 36mo)

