Data for this aim will be extracted from the EHR, as summarized in Table 1. The primary outcome for Aim 1 is prediabetes or T2DM. A participant will be considered to have a clinical diagnosis of prediabetes if they have a hemoglobin A1C level ≥ 5.7% and < 6.5% measured at the time of the clinic visit. A participant will be determined to have T2DM if they have any one of the following: an A1C ≥ 6.5%, a prior history of T2DM based on ICD-10 codes in the EHR, and/or currently taking a diabetic medication (including glucagon-like peptide 1 receptor agonist, sodium-glucose cotransporter 2 inhibitor, dipeptidyl peptidase 4 inhibitor, sulfonylurea, incretin mimetic, or insulin).

##### Power and sample size for Aim 1

We anticipate accruing 1800 patients (~ 90% of the clinic population) to complete the baseline assessment. These participants will be followed for up to 3 years with an expected loss to follow-up of 15%. Rates of food insecurity in the overall population in our region are 15–20%. In our previous weCare study, about 27% of participants needed support services for food in the past 6 months; in addition, 57% of the clinic population is below 100% of the federal poverty level. Therefore, we assume that 30% of this sample will be food insecure (*n*=540). Based on available data of PWH [55], we expect the baseline prevalence of prediabetes/T2DM in the food-secure group to be 25% at baseline. Under these assumptions, we will have 80% power to detect a difference between a baseline prevalence of prediabetes/T2DM of 25% among non-food-insecure participants and a prevalence of 31.6% (odds ratio=1.38) among food-insecure participants using a two group *χ*^2^ test with a 5% two-sided significance level. Assuming that 75% of the sample will not have prediabetes/T2DM at baseline, the sample size for estimating incidence is *n* = 1350. Based on a study by Nansseu et al. of PWH, we assume the incidence of prediabetes is 125 per 1000 person-years and the incidence of T2DM is 13.7 per 1000 person-years [56]. We then have 80% power to detect a prediabetes incidence rate ratio of 1.7 between those with and without food insecurity and a T2DM incidence rate ratio of 3.7, using a log-rank test for two survival curves with a 5% two-sided significance level.

##### Analysis plan for Aim 1

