The two groups will be compared with a weighted generalized log-rank test. Next, we will fit proportional hazards regression models for interval-censored data using PROC ICPHREG that will allow us to adjust for potential confounders and include time-varying covariates. Participants will be included in the analysis up until the end of their follow-up (the last time they have an in-person visit) or the first visit in which they are diagnosed with prediabetes or T2DM. For individuals diagnosed with prediabetes at baseline or during the follow-up, we will estimate the incidence of transitioning to diabetes using similar survival models. We will explore the prevalence and incidence of other secondary cardiometabolic comorbidities using similar analyses. We will also use linear mixed effects regression models to estimate trends in A1C and other continuous indicators of cardiometabolic comorbidities (secondary outcomes) over time accounting for the correlation of repeated measures using a random intercept model. We will test for difference in trends (slopes) between food-secure and insecure individuals using *F*-tests. These models will be fit using SAS PROC MIXED.

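### Aim 1 secondary trend analyses: the slope comparison uses a random-intercept-only model, which makes the F-test anti-conservative if participants' own slopes vary materially and there are three or more annual visits

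*Protocol article*

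**What the plan says.** The protocol article, under Analysis plan for Aim 1, uses linear mixed models to "estimate trends in A1C and other continuous indicators of cardiometabolic comorbidities (secondary outcomes) over time". The covariance model is given as "accounting for the correlation of repeated measures using a random intercept model". The hypothesis follows directly: "We will test for difference in trends (slopes) between food-secure and insecure individuals", by F-test. On software it says "These models will be fit using SAS PROC MIXED".

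The measurement schedule is in the Aim 1 Data collection section: "data will be collected at baseline and at 12-, 24-, and 36-month follow-up". Power and sample size for Aim 1 plans 1800 participants, and "we assume that 30% of this sample will be food insecure", which gives 540 food-insecure and 1260 food-secure. It expects 15% loss to follow-up. No power, significance level, slope SD or residual SD is given for the slope test.

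**The concern.** A random intercept lets participants differ in level only. It assumes that everyone in a group shares one underlying slope and that the correlation between any two visits is the same whether they are one year or three years apart. The quantity tested is a difference in slopes, so between-person variation in slopes is part of its sampling error. If that variation exists, the model captures only a fraction of it.

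Varying slopes are plausible here. The cohort mixes people without diabetes, with prediabetes and with T2DM, and the plan itself expects incident prediabetes at 125 per 1000 person-years. Participants also differ in glucose-, lipid- and blood-pressure-lowering medication. In addition, 100 Aim 1 members, all food insecure, are to be randomized in Aim 2 to an intervention meant to improve insulin sensitivity.

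At stake is the error rate of the secondary trend comparisons. Standard errors that are too small would produce too many apparent slope differences and confidence intervals that are too narrow. Sample size does not cure this, because the true and the model-based variances shrink at the same rate.

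**Working it through.** The plan states no figure for this test, so there is none to reproduce.

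**Inputs from the protocol.** Visits at 0, 1, 2 and 3 years; groups of 540 and 1260; 15% loss to follow-up; random intercept only.

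**Inputs assumed.** A two-sided 5% level; residual SD *s*; SD *τ* of participants' own slopes per year, similar in both groups; *q* = *τ*/*s*.

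**Formulas.** With *T* equally spaced visits, let Sxx be the sum of squared deviations of time from its mean.
- True variance of one participant's estimated slope: *s*²/Sxx + *τ*².
- The random-intercept model pools slope variation into its residual variance, which becomes *s*² + *τ*²·Sxx/(*T* − 1). It therefore uses *s*²/Sxx + *τ*²/(*T* − 1).
- With *R* = true/model variance, the actual type I error is 2[1 − Φ(1.96/√*R*)].

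**Four visits.** Sxx = 2.25 + 0.25 + 0.25 + 2.25 = 5, so *R* = (0.2 + *q*²)/(0.2 + *q*²/3). The model counts one third of the slope variance.

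| *q* | *R* | SE ratio √*R* | Type I error |
|---|---|---|---|
| 0.1 | 0.2100/0.2033 = 1.03 | 1.02 | 5.4% |
| 0.2 | 0.2400/0.2133 = 1.13 | 1.06 | 6.5% |
| 0.3 | 0.2900/0.2300 = 1.26 | 1.12 | 8.1% |
| 0.5 | 0.4500/0.2833 = 1.59 | 1.26 | 12.0% |

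On an A1C scale, with assumed *τ* of 0.1 to 0.2 points per year and *s* of 0.3 to 0.5 points:
- *s* = 0.5: *τ* = 0.1 gives 6.5%; *τ* = 0.2 gives 10.0%.
- *s* = 0.3: *τ* = 0.1 gives 8.7%; *τ* = 0.2 gives 15.0%.

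**Three visits.** Sxx = 2, so the true variance is *s*²/2 + *τ*² and the model uses *s*²/2 + *τ*²/2.
- Lowest (*τ* = 0.1, *s* = 0.5): *R* = 0.135/0.130 = 1.04, type I error 5.4%.
- Highest (*τ* = 0.2, *s* = 0.3): *R* = 0.085/0.065 = 1.31, type I error 8.7%.

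**Two visits.** *T* − 1 = 1, so *R* = 1 and there is no inflation.

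**Simulation check.** REML random-intercept fits used 1800 participants split 540/1260, four visits, 15% monotone dropout, no true slope difference and 1500 replicates per setting. Rejection rates were 5.7% at *q* = 0, then 5.1%, 6.5%, 7.7% and 12.9% at *q* = 0.1, 0.2, 0.3 and 0.5. At *q* = 0.5 the mean model SE was 0.0289 against an empirical SD of 0.0374. This agrees with the closed form within simulation error.

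**Unequal slope variance (four visits, closed form).** If only the larger food-secure group has varying slopes, type I error is 5.3% at *q* = 0.3 and 5.7% at *q* = 0.5. If only the food-insecure group does, it is 8.1% and 12.9%.

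**The case against.** The strongest reply is about size and scope, and much of it stands.

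- **Scope.** The trend models are labelled secondary and carry no power claim. The Aim 1 primary outcome, prediabetes or T2DM, is analysed by chi-square, logistic and interval-censored survival methods. The Aim 2 primary analysis is an ANCOVA at one follow-up time. A reader might infer that the study's main conclusions are at risk; the document does not support that.
- **Size.** No slope SD or residual SD is given for any outcome, so no particular error rate can be claimed. At *q* = 0.1 the inflation is negligible. A reader might infer that the 5% level and the intervals are wrong as a matter of fact, or that any slope variation at all inflates the error. Neither follows: the inflation needs three or more visits and slope variance that is material relative to residual variance.
- **Level.** The 5% level is stated for the chi-square and log-rank tests, not for this F-test.
- **Left to the SAP.** Covariance detail often sits there. That defence is only partial, because the article does not stay silent: it names one covariance model and pairs it with a slope test.

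Staggered entry, with some participants reaching only two or three visits, does not remove the problem. Suppose one third each have two, three and four visits (Sxx 0.5, 2 and 5). Mean Sxx is 2.5, mean Sxx² is 9.75 and mean *T* − 1 is 2. Using within-person information only, *R* = (0.4 + 1.56*q*²)/(0.4 + 0.5*q*²). This gives 6.2% at *q* = 0.2 and 11.0% at *q* = 0.5.

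**Conclusion.** The point holds in conditional form, for the Aim 1 secondary trend analyses only. The stated model suits a comparison of levels better than a comparison of slopes. If slopes vary materially, its standard error is too small and the F-test rejects too often.

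The direction is well established for three or more visits when slope variance is similar in the two groups, and it was also upward in every unequal-variance case tried. The size is not established. It runs from practically nothing to more than double the assumed 5% level, depending on a variance ratio that the protocol does not give. This is worth correcting because the same model is applied to several outcomes and the remedy is cheap, but it does not threaten a primary conclusion.

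**What to change.** In PROC MIXED, add a random slope for time alongside the random intercept, with an unstructured covariance between the two, or use an unstructured covariance over the visits. If neither converges, keep the random intercept but report empirical (sandwich) standard errors. State the significance level for the slope F-test.

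The change is about one line of code, and four annual visits in a cohort of this size should support the extra variance parameters. The cost is wider confidence intervals for the slope difference. From the four-visit table, the widening would be about 2%, 6%, 12% and 26% at *q* = 0.1, 0.2, 0.3 and 0.5. If slopes hardly vary, little is lost.

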#### Aim 2: Implement and test weCare/Secure to determine the impact of the intervention on insulin sensitivity among food-insecure PWH with prediabetes or T2DM using an RCT

##### Participants

The participants in Aim 2 will be a subset of Aim 1 participants who enrolled in year 1. From potentially eligible participants identified by EHR data extracted in Aim 1, we will randomly select participants to invite to enroll in Aim 2, starting in year 2. To be eligible to participate in Aim 2, a participant must (a) be a patient of the Wake Forest Infectious Diseases Specialty Clinic, (b) be living with HIV, (c) be receiving antiretroviral therapy (ART) for ≥ 3 months, (d) be ≥18 years of age, (e) screen as food insecure, (f) have prediabetes or T2DM, and (g) provide informed consent. Access to a smartphone will not be an inclusion criterion because participants may communicate with the peer navigator via mHealth platforms accessible on a computer (e.g., Facebook messenger) at their home or in community spaces such as the public library. PWH will be excluded if they are unable to speak English or Spanish, are currently pregnant, are receiving chronic treatment with systemic corticosteroids (similar exclusion as the Look AHEAD Trial, which evaluated the effects of an intervention designed to promote weigh loss among overweight and obese individuals with T2DM [57]), have type 1 diabetes, and/or have cognitive impairment that would prevent participation.

If participants are eligible and consent to participate, they will then complete Aim 2 baseline data collection as outlined in Table 1. After these data are collected, they will be randomly assigned into weCare/Secure (*n*=100) or usual care (*n*=100). Those randomized to the weCare/Secure intervention will receive the intervention for 6 months. For random selection and assignment, our statistician will use block randomization with a randomly selected block size. The research coordinator will enroll, consent, and assign participants to groups. We will continue this process until we reach our sample size of 200. Participants may discontinue participation in the intervention at any time. Given the behavioral nature of the intervention, there will be no other special criteria for discontinuing or modifying allocated interventions. Aim 2 participants will be compensated $40 at baseline and $60 at 6-month follow-up.

##### Intervention overview

In this intervention, the peer navigator will use the mHealth platforms preferred by each participant (i.e., Facebook, Instagram, WhatsApp, texting, and/or GPS-based mobile apps) to communicate one-on-one with each participant in English or Spanish during the 6-month intervention. The peer navigator’s approach is personalized to the needs and priorities of each participant. Table 2 provides an abbreviated summary of peer navigator roles and examples of each role operationalized. The potential for immediate, efficient, and bidirectional in-real-time communication between a peer navigator and each participant is critical to overcome barriers associated with taking action, initiating and maintaining use of food-related resources, and obtaining improved health outcomes, related to both HIV and cardiometabolic disease. Refined messages will be organized by needs (e.g., seeking a food resource such as a pantry; applying for SNAP benefits; overcoming stigma related to food insecurity, sexual or gender identity, and/or HIV; or problem-solving challenges to preparing healthy foods) and by theoretical construct.

**Table 2 Tab2:** Roles of the peer navigator

Roles	Examples
Check-in	Checks in with the participant periodically to build rapport and trust, provide social support, and maintain bidirectional communication.
Provide information and referrals	Provides information about resources for food. If the referral is to a social service or benefit, the peer navigator will provide information about whether an appointment is needed and if so how to make one.
De-mystify accessing available community-based resources	Explains what to expect when accessing resources, including where to go, transportation options, sign-in processes or the presence of security guards, and whom to ask for.
Explain how to navigate resources and benefits	Explains how to apply for benefits and what materials are needed when applying for SNAP/WIC/TANF benefits.
Send announcements and reminders	Notifies participants of time-sensitive opportunities to access food resources (e.g., a mobile food pantry visiting a specific neighborhood).
Troubleshoot and problem solve	Identifies options for overcoming barriers (e.g., transportation).
Support healthy eating	Provides guidance on shopping for healthy foods on a limited budget and preparing foods according to recommendations for reducing cardiometabolic disease risks (e.g., cooking methods to preserve the nutrient content of vegetables and seasoning foods without high levels of sodium).
Support provider communication	Talks through ways for the participant to share concerns with providers about food insecurity, HIV care, and cardiometabolic disease, including challenges to dietary changes or other cardiometabolic disease management strategies.

##### Usual care

Currently, the standard of care in the Wake Forest Infectious Diseases Specialty Clinic for PWH identified as food insecure is to have them meet with a clinic social worker and review options for food access, such as local food pantries. A resource list is also provided to the PWH. As indicated, referrals for social services may be made. There is no peer navigation within usual care. All participants, those in the weCare/Secure arm and in the usual care arm, will receive usual care. As such, implementing the intervention does not require alteration to usual care pathways (including medication use) and these will continue for both trial arms.

##### Monitoring adherence

The peer navigator will meet with each participant in person at the beginning of their participation in the intervention (after enrollment) to build rapport and lay a foundation of trust that builds during intervention implementation to improve adherence to the intervention. Growing evidence suggests that in-real-time, personalized, and bidirectional social support and problem solving provided by a peer navigator using mHealth may be more successful in changing complex behaviors and behaviors among populations with greater barriers to change (e.g., populations with stigmatized characteristics and/or needs) than a “bot,” a software application structured to provide social media-based messages automatically [46]. We will also conduct process evaluation to document intervention delivery. The peer navigator will maintain a log of their interactions with weCare/Secure participants to capture the mode of intervention delivery, dose, and messaging for each participant (e.g., which mHealth platforms were used, who initiated contact [the participant or peer navigator], the dates and times that messages were sent, number of messages exchanged, and the types of messages utilized to communicate with each participant).

##### Data collection

The quantitative assessment will collect demographic, cognitive, behavioral, psychosocial, and socioeconomic data at baseline and post-intervention follow-up using REDCap (Research Electronic Data Capture), a secure web application for building and managing online surveys and databases maintained by Wake Forest University School of Medicine. Selection of other constructs are guided by the underlying theories and literature describing factors influencing food insecurity and cardiometabolic comorbidities (as highlighted in Fig. 1).

Table 1 provides measurement priorities identified while preparing the application for this study. The assessment, including final selection of measures, will be created using an iterative process by the research team in collaboration with a project-specific community steering committee comprised of community members (including PWH) and representatives from community organizations that provide services related to HIV and to food security. The assessment will be translated into Spanish by a native Spanish speaker trained in professional translation. Participants will complete the quantitative assessment on a tablet while attending baseline and post-intervention (6 months post-baseline) study visits at the clinic.

Our primary outcome for Aim 2 is the difference in mean difference homeostatic model assessment of insulin resistance (HOMA-IR) score between intervention and control arm participants at 6 months, controlling for baseline HOMA-IR is capable of measuring small changes in insulin sensitivity, especially among PWH and persons with prediabetes [58, 59]. At each study visit, fasting glucose and fasting insulin levels will be measured to calculate participants’ HOMA-IR score by venous blood sample. The blood sample will not be stored for future use.

For our secondary outcomes, we will assess for change in food security and change in the pathways (nutrition, mental health, and behavioral; Fig. 2) proposed to influence food insecurity and cardiometabolic comorbidities from baseline to 6-month follow-up (Table 1). To measure the change in food security over a 6-month period, we will use the 18-item USDA Food Security Survey Module (FSSM) 30-day questionnaire, in addition to the 2-item Hunger Vital Sign assessment. The 30-day questionnaire assesses food insecurity over the prior month and successfully assesses changes in food security over time [53, 54].

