##### Process data collection

We will also conduct process evaluation to document intervention delivery. The peer navigator will maintain a log in REDCap of their interactions with weCare/Secure participants to capture the mode of intervention delivery, dose, and messaging for each participant (e.g., which mHealth platforms were used, who initiated contact [the participant or peer navigator], the dates and times that messages were sent, number of messages exchanged, and the types of messages utilized to communicate with each participant).

##### Power and sample size for Aim 2

Assuming 100 participants are randomized to the intervention arm and 100 to the usual care arm, we will have 80% power to detect a difference in the mean change in HOMA-IR between arms of 0.54, assuming a standard deviation of 1.5 (based on unpublished data from our clinic) and a correlation of 0.6 between baseline and follow-up assessments.

##### Analysis plan for Aim 2

We will use a longitudinal RCT with 2 arms (intervention and usual care) to evaluate the impact of the intervention. Data will be analyzed as an intent-to-treat study [60]; with electronic health data, we do not expect much missing data (at any of the time points) so we do not plan to use data imputation techniques. First, we will compare the characteristics of participants assigned to the intervention and usual care arms using *t-*tests for continuous covariates and *χ*^2^ tests for discrete covariates. Our primary data analysis will compare mean HOMA-IR levels for the intervention and usual care arm participants at the 6-month follow-up assessment adjusting for baseline levels. This follow-up adjust baseline approach has the advantage of being unaffected by baseline differences. If baseline rates, by chance, were different in the intervention arm, the intervention effect would be overestimated by looking at change scores and underestimated by a follow-up score analysis. The ANCOVA approach gives the same answer whether or not there is baseline imbalance. Additionally, this approach generally has greater statistical power to detect an intervention effect than the other methods. Statistical analyses will be performed using linear models for continuous outcomes in SAS PROC GLM.

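### Aim 2's primary outcome, HOMA-IR, is calculated from measured fasting insulin, but insulin-treated participants are eligible and enter the primary analysis with no provision for them

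*Protocol article*

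**What the plan says.** - **Outcome.** Aim 2, Data collection: at each study visit "fasting glucose and fasting insulin levels will be measured to calculate" HOMA-IR. The measure is supported there as "capable of measuring small changes in insulin sensitivity, especially among PWH and persons with prediabetes". Insulin-treated T2DM is not discussed.
- **Who has T2DM.** Aim 1, Data collection: any one of three criteria suffices, and one is current use of a diabetic medication, in a list that ends "dipeptidyl peptidase 4 inhibitor, sulfonylurea, incretin mimetic, or insulin".
- **Who enters Aim 2.** Aim 2, Participants: candidates are found from the Aim 1 EHR extraction and must "f) have prediabetes or T2DM, and (g) provide informed consent". The exclusions are language, pregnancy, chronic systemic corticosteroids, and those who "have type 1 diabetes, and/or have cognitive impairment that would prevent participation". Insulin use is not among them.
- **Care during the trial.** Usual care, including medication, continues in both arms (Usual care). Participants and the peer navigator are not blinded (Blinding).
- **Analysis.** Analysis plan for Aim 2: by intent to treat, the primary analysis will "compare mean HOMA-IR levels for the intervention and usual care arm participants at the 6-month follow-up assessment adjusting for baseline levels", using a linear model in PROC GLM. No transformation and no term for insulin use is stated.
- **Power.** Power and sample size for Aim 2: 100 per arm, 80% power, difference 0.54, SD 1.5 from unpublished clinic data, correlation 0.6.

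**The concern.** HOMA-IR rises with both fasting glucose and fasting insulin. In someone who takes insulin, the measured insulin can be partly the drug. A high score may then reflect treatment, and a change in score may reflect a change of treatment. Three things are at stake.

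1. **Meaning.** For these participants the primary outcome is not a clean measure of insulin sensitivity, which is what Aim 2 sets out to change.
2. **Precision.** A minority with much larger and more variable scores can supply a large part of the variance of an untransformed mean difference.
3. **Possible bias.** The peer navigator supports communication with providers about managing cardiometabolic disease (Table 2), and diabetes self-care is a measured pathway (Table 1). Insulin treatment or adherence could therefore change differently by arm, and the score would move without any change in insulin sensitivity.

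Table 1 schedules extraction of diabetic medication at baseline and 12, 24 and 36 months, so the 6-month visit has no planned record against which to check the third point.

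**Working it through.** **Inputs from the article:** n = 100 per arm, SD 1.5, correlation 0.6, 80% power, difference 0.54. The Aim 2 power paragraph gives no alpha, so 5% two-sided is assumed.

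**Step 1: the plan's own figure.**
- Change score: SD = 1.5 × √(2 × (1 − 0.6)) = 1.342. Detectable difference = (1.96 + 0.8416) × 1.342 × √(2/100) = 0.53 (0.534 with the t distribution). Power at 0.54 is 0.81, so the stated figure reproduces.
- Planned ANCOVA: residual SD = 1.5 × √(1 − 0.6²) = 1.2. Detectable difference = 0.475 (0.478 with t), power at 0.54 = 0.89. The stated 0.54 is therefore conservative for the planned model.

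**Step 2: add insulin users.** The article gives no share or distribution for them. Assume non-users have mean 3 and SD 1.5, users have mean 9 and SD 4.5, within-group correlation is 0.6, and users remain users. For a share p of users:
- within-group variance W = (1 − p) × 1.5² + p × 4.5²
- between-group variance B = p(1 − p) × 6²
- overall correlation r = (0.6W + B)/(W + B)
- ANCOVA residual SD = √((W + B)(1 − r²))

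The user/non-user gap is present at both visits. It therefore raises r, and the baseline adjustment absorbs part of it.

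| p | W | B | Total SD | r | Residual SD | Detectable difference (t) | Power at 0.54 |
|---|---|---|---|---|---|---|---|
| 0 | 2.25 | 0 | 1.50 | 0.60 | 1.20 | 0.48 | 0.89 |
| 2% | 2.61 | 0.71 | 1.82 | 0.69 | 1.33 | 0.53 | 0.82 |
| 5% | 3.15 | 1.71 | 2.20 | 0.74 | 1.48 | 0.59 | 0.73 |
| 10% | 4.05 | 3.24 | 2.70 | 0.78 | 1.70 | 0.68 | 0.61 |

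Example at 5%: r = (0.6 × 3.15 + 1.71)/4.86 = 3.60/4.86 = 0.741; residual SD = √(4.86 × (1 − 0.549)) = 1.48; detectable difference = 0.478 × 1.48/1.2 = 0.59.

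**Step 3: possible bias.** If insulin starts or stops differ between arms by 5 percentage points, and each shifts HOMA-IR by 3 to 10 units (both assumed), the contrast moves by 0.05 × 3 = 0.15 to 0.05 × 10 = 0.50, against a target of 0.54. With no difference between arms in insulin changes, the shift is zero.

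**Step 4: scale.** In lognormal simulations (100 per arm, correlation 0.6, 3,000 runs), type I error of the untransformed ANCOVA was 0.044 to 0.054. With an effect equal to 0.54 at the mean, power untransformed against log was 0.94 and 0.97 at mean 3/SD 1.5, and 0.45 and 0.63 at mean 3/SD 3. Skewness costs power and precision, not validity of the test. The cost is small if the SD of 1.5 is right and larger if the distribution is wider.

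**Step 5: removing users from the primary set.** With 90 per arm and residual SD 1.2, ANCOVA power at 0.54 is 0.85.

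**The case against.** **Randomisation balances baseline insulin use in expectation.** This stands. Bias needs insulin changes that differ by arm, and the article gives no evidence of them. They are possible in an open-label trial with unrestricted medication, but not shown.

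**The SD of 1.5 may already include insulin users.** This also stands. The article does not say. If it does include them, the table above counts their variance twice, and 0.48 remains the ANCOVA figure. A reader might infer that the stated power cannot be reached; the article does not support that. At 2% users the assumed model still gives 0.82 power at 0.54.

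**Baseline adjustment removes much of the added variance.** It does. A reader might scale the detectable difference by the total SD alone. That would hold the correlation at 0.6 and overstate the loss, because the persistent gap between users and non-users raises r.

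**The support for HOMA-IR is not limited to prediabetes.** Correct. Its wording singles out PWH and prediabetes without excluding others, and every participant is a PWH. It still says nothing of insulin-treated T2DM.

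**Transformation and covariates may sit in an unseen SAP.** Fair. Their absence is not an error in the article, and the recommendations on them are improvements. The difficulty with insulin users is different, because the article itself fixes eligibility, outcome and intent-to-treat inclusion.

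**Restricting to baseline non-users narrows the population and leaves in anyone who starts insulin later.** Both are true, so the all-randomised analysis and a 6-month record of insulin use are needed beside it.

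**Conclusion.** The point holds. As written, the plan scores some eligible participants on a HOMA-IR value that can partly reflect administered insulin, and it includes them in the primary contrast without distinction. The certain consequence is an outcome with unclear meaning in those participants. Added variance is likely, and bias is conditional on insulin changes that differ by arm.

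Under the stated assumptions, the ANCOVA detectable difference rises from 0.48 to about 0.59 with 5% users and 0.68 with 10%, against the planned 0.54. The true size is unknown, because the article gives neither the share of users nor the make-up of the data behind the SD of 1.5. A reader might also infer that comparing untransformed means makes the test invalid. It does not: the means are baseline-adjusted, and simulated type I error stayed close to 5%.

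**What to change.** Before outcome data are examined:

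1. Define the primary HOMA-IR analysis set as randomised participants not using insulin at the Aim 2 baseline. Because the set is defined at baseline, it keeps the randomised comparison. Confirm insulin status at that visit, since the Aim 1 extraction precedes it. Report the all-randomised analysis alongside as a sensitivity analysis. Eligibility and care do not change.
2. Analyse log(HOMA-IR) adjusted for log baseline HOMA-IR, and report the ratio of geometric means.
3. Adjust for baseline diabetes status (prediabetes or T2DM) and baseline glucose-lowering medication, both already collected.
4. Extract insulin use from the EHR at 6 months as well, and run a sensitivity analysis for insulin started after baseline.
5. State whether the SD of 1.5 came from data that included insulin users, and restate the power for the set analysed.

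**Cost.** One added EHR extraction, otherwise analysis wording. The primary set is somewhat smaller (ANCOVA power about 0.85 at 0.54 with 90 per arm, if the stated SD holds) and describes a narrower population, and the effect is reported as a ratio. A1C should not be assumed to be available as a 6-month substitute in insulin users, because Table 1 does not schedule it then.
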